### Sample Size Calculation

This pilot study (n=30 in each of the two groups) will examine the differences in biological measures to perform power calculations for a larger study. This will also serve as a feasibility study to determine the feasibility of applying GPS, GIS, and EMA for a larger sample of adults. A sample size of 30 per group allows for estimation of the SD of the amygdala FDG in each group, with an upper bound on the SD 20% larger than the estimate, based on the normal distribution large sample 90% upper confidence bound of:

where 
[figure not shown]
 is the 10% quantile of the chi-squared distribution with n−1 degrees of freedom and s is the SD estimate. We plan to recruit approximately 90 participants, assuming that approximately 20% of participants will be lost to follow-up during the study.

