**Methods:**

The proposed study will be cross-sectional, with a sample of at least 60 women (30 healthy White women and 30 healthy Black women) from Wards 3 and 5 in Washington, DC. A sample of the women (n=30) will be recruited from high-income areas in Ward 3 from census tracts within a 15% of Ward 3’s range for median household income. The other participants (n=30) will be recruited from low-income areas in Wards 5 from census tracts within a 15% of Ward 5’s range for median household income. Finally, participants from Wards 3 and 5 will be matched based on age, race, and BMI. Participants will wear a GPS unit and accelerometer and report their stress and mood in real time using a smartphone. We will then examine the associations between GPS-derived neighborhood variables, stress-related neural activity measures, and adverse biological markers.

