### Study Participants

A sample of women (at least n=30; 15 White women and 15 African American women) will be recruited from higher SES census tracts within a 15% range of the median household income in Ward 3 (median household income=US $126,184) [30]. The other participants (at least n=30; 15 White women and 15 African American women) will be recruited from lower SES census tracts within a 15% range of the median household income in Ward 5 (median household income=US $68,375) [31]. Participants from Wards 3 and 5 will be matched based on age, race, and BMI.

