### Schedule of Events

Participants will visit the NIH Clinical Center where we will instruct them on how to use the devices and measurement tools (accelerometer, GPS, and EMA; Table 1). During the inpatient visit, we will conduct a cardiovascular examination, draw blood, and conduct a vascular stiffness test. Participants will also undergo 18F-FDG-PET/CT testing to measure chronic stress–related neural activity (ie, amygdala brain activity) and vascular inflammation. On the first day of the inpatient visit, study volunteers will follow a controlled eucaloric diet containing 55% carbohydrate, 15% protein, and 30% fat and providing 150% of their estimated resting energy needs in preparation for testing to accurately measure energy expenditure on inpatient day 2. Resting energy expenditure has not been included in the aims of this study. However, this measure can be evaluated as a moderator for the sub-aims of aims 1 and 2.

**Table 1 table1:** Schedule of events.

Events				First Clinical Center visit					At least 14-day monitoring			2nd Clinical Center visit
				Day 1		Day 2						
Recruitment				Ongoing		Ongoing		Ongoing			Ongoing	
Informed consent				✓								
Vital signs				✓								
Anthropometric measures				✓								
Clinical blood testing				✓							✓	
Cardiovascular examination				✓							✓	
Blood pressure				✓							✓	
Blood glucose				✓							✓	
Hemoglobin A_1c_				✓							✓	
Lipid panel				✓							✓	
Resting energy expenditure						✓						
18-fluorodeoxyglucose positron emission tomography-computed tomography						✓						
Pulse wave velocity				✓								

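### The recruitment target of about 90 does not follow from 60 women and 20% loss, the only reason given for it

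*Protocol article*

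**What the plan says.** The Sample Size Calculation section sets the group size: "This pilot study (n=30 in each of the two groups) will examine the differences in biological measures". It justifies that size by precision, not power: "A sample size of 30 per group allows for estimation of the SD of the amygdala FDG in each group", with a 90% upper confidence bound about 20% above the estimate. The recruitment target follows: "We plan to recruit approximately 90 participants, assuming that approximately 20% of participants will be lost to follow-up during the study".

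The minimum is stated in the same terms elsewhere. The Abstract describes a cross-sectional study "with a sample of at least 60 women". Study Participants divides each ward by race, for example "A sample of women (at least n=30; 15 White women and 15 African American women" from Ward 3, with the same numbers for Ward 5. That makes four cells of at least 15.

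On timing, Schedule of Events says of the inpatient visit: "Participants will also undergo 18F-FDG-PET/CT testing to measure" stress-related neural activity. Table 1 places the scan on Day 2 of the first visit. The device period of at least 14 days comes after visit days 1 and 2. The second visit repeats blood tests and the cardiovascular examination but has no PET/CT.

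**The concern.** Three numbers in one section (30 per group, about 20% loss, about 90 recruits) are presented as a chain, and the last link does not follow. A reader cannot tell whether the loss rate, the target or an unstated allowance accounts for the difference.

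This matters for two reasons. First, the surplus falls on healthy volunteers, who are asked to accept an inpatient stay and an FDG-PET/CT scan. Second, the study is a pilot meant to supply planning figures and feasibility evidence for a larger one. If the investigators in fact expect to lose a third of recruits, that expectation is itself a planning figure and is not disclosed.

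**Working it through.** **Inputs**, all from the article:
- Required n: 30 per ward, 60 in total (Sample Size Calculation; Abstract, Methods).
- Cells: at least 15 women in each of four ward-by-race cells (Study Participants).
- Loss: d = 0.20 (Sample Size Calculation).
- Target: about 90 (same section).

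**Step 1. Check the starting n.** The section names the 10% quantile of the chi-squared distribution on n−1 degrees of freedom. The bound as a multiple of s is √[(n−1)/χ²₀.₁₀,ₙ₋₁].
- At n = 30 this gives 1.211.
- A large-sample form, 1/[1 − z₀.₉₀/√(2(n−1))], gives 1.202.

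The stated bound of about 20% is therefore reproduced, and n = 30 per group stands.

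**Step 2. Try to reproduce 90.** The standard inflation is N = n/(1−d). The cruder form is n(1+d).

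| Basis | n/(1−d) | n(1+d) |
|---|---|---|
| Total of 60 | 60/0.80 = 75 | 60 × 1.20 = 72 |
| Per ward, 30 × 2 | 37.5, rounded to 38; × 2 = 76 | 36 × 2 = 72 |
| Per cell, 15 × 4 | 18.75, rounded to 19; × 4 = 76 | 18 × 4 = 72 |

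No entry is near 90. The gap is 90 − 76 = 14 to 90 − 72 = 18 women, too wide for the word approximately to cover.

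**Step 3. Work back from 90.**
- At 20% loss: 90 × 0.80 = 72 retained, or 36 per ward if evenly split.
- Loss implied by ending at 60: 1 − 60/90 = 33.3%.
- Extra loss needed on top of the stated 20%: 1 − 75/90 = 16.7%.
- Two successive 20% losses: 60/(0.80 × 0.80) = 93.75. This is near 90, but the article states only one.

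**Step 4. Effect on precision.** With 36 per group, the bound from Step 1 is 1.188 (1.181 by the large-sample form), that is, 18% to 19% above the estimate. The surplus tightens the SD estimate slightly and puts nothing at risk.

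**Step 5. Where the loss falls.** Amygdala FDG is measured on Day 2, before monitoring starts, and is not repeated. A woman lost during monitoring has normally been scanned already. What her loss removes is GPS, EMA and accelerometer data and the second blood draw.

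**The case against.** The best defence is that nothing is endangered. The article speaks of at least 60 women, and 72 completers meet every stated minimum. This stands. A reader might infer that the three numbers cannot all hold, but that goes too far: 90 is an unexplained surplus over a floor, not a strict contradiction.

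A reader might also fault the 20% bound because the chi-squared quantile gives 21%. That is not supported. The displayed formula is missing from the available text, the section describes a large-sample bound, and a large-sample form gives 20.2%. The difference is rounding.

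A third tempting inference is that 90 recruits means 45 scans per group. The article says recruit, not scan. Consent, measurements and blood tests are on Day 1, and several exclusions (BMI, blood pressure, thyroid disease) could come to light then, so some women may leave before the Day 2 scan. An even split is also uncertain: the Limitations section expects difficulty recruiting African American women in Ward 3. The excess of about 15 is therefore a ceiling.

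Finally, one might say that the loss allowance is misapplied because the scan precedes follow-up. The article does not say that the 20% protects the FDG estimate. It refers to loss during the study, and the GPS, EMA and accelerometer models and the second blood draw do lose women, so a study-wide allowance is legitimate.

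None of this supplies the missing step. Losses before the scan, failed matching or unusable data could explain 90, but the section gives only the 20%.

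**Conclusion.** The concern holds as a derivation error in one sentence. With 60 women required and 20% loss, the target is 75, or 76 with equal wards or cells. The stated 90 is 14 to 15 higher and would match a loss of 33%. The error is in the safe direction for the statistics: the minimum sample and the SD precision are both secure. The cost is that up to about 15 healthy women beyond what the stated reason supports could have the inpatient visit and scan, or else that a larger expected loss goes unstated.

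This rests on reading 30 per group as the number to be retained and the 20% as the whole allowance, which is how the section presents them. The timing of the scan is not a second error. It only qualifies which analyses the 20% mainly affects.

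**What to change.** In the Sample Size Calculation section, do one of the following:
- Restate the target as about 76 for 20% loss (19 in each of four ward-by-race cells).
- Keep 90 and state the further losses, such as ineligibility or withdrawal before the scan or unusable data, that bring the total to about 33%.
- Keep 90 and state that about 72 completers are expected (36 per group if evenly split), with an SD bound of about 19%.

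In each case, add that FDG-PET/CT is done on Day 2 of the first visit, so the 20% loss mainly affects the device-dependent analyses and the second blood draw. The 20% bound quoted for 30 per group can stay.

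The cost is two or three sentences, with no added participants and no change to the analysis.

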### Plans for Data Management

The NHLBI IRB has approved this protocol. The data with patient identifiers will be securely stored in the eHealth and data management systems at the NIH, which are protected by passwords and data encryption. These data will be shared only with approved members of the research team. The entire data set for the participants included the clinical information, GPS or accelerometer data, data through the EMA mobile app, and survey data.

A Food and Drug Administration–approved biospecimen tracking inventory system will be used to securely store all collected biological specimens at the NIH. The NIH IRB will review and approve any future testing of undefined biospecimens in the protocol before any data collection. The participants are allowed to refuse future use.

This research is scheduled to begin in 2021, with plans for completion by 2023. However, because of the COVID-19 pandemic, it may be delayed depending on the current pandemic situation. Participants who receive unintended consequences from study participation will be treated according to best practices under the NIH Clinical Center. This study is low risk; thus, it does not require a data monitoring committee. The principal investigator will monitor accrual and safety data. The protocol will be reviewed and monitored annually by the IRB and the NHLBI Office of the Clinical Director’s Protocol Audit Team, along with any amendments requiring IRB approval. The results and conclusions of this research will be disseminated to community members through DC-CHOC meetings and a quarterly newsletter as well as at national and international conferences and in peer-reviewed publications.

## Results

### Feasibility of GPS Use

We tested the feasibility of using a GPS device and an EMA app with 11 participants from a PA-related study among African American women (ClinicalTrials.gov identifier NCT03288207). The mean age of the women was 56 years, and most of the participants had at least a high school education (Table 4). The majority of participants had a total household income of US $60,000-89,999; were employed part-time; and resided in Prince George’s County, Maryland.

**Table 4 table4:** Sociodemographic characteristics of participants (N=11).

Participant characteristics			Values
Age (years), mean (SD)			56.3 (12.3)
Gender (female), n (%)			11 (100)
**Race, n (%)**			
	Black or African American	11 (100)	
**Education, n (%)**			
	College degree	4 (36)	
	Graduate or professional school degree	3 (27)	
	Some college degree	2 (18)	
	High school diploma or Tests of General Education Development	1 (9)	
	Some graduate or professional school	1 (9)	
**Total household income (US $), n (%)**			
	20,000-59,000	3 (27)	
	60,000-89,999	5 (46)	
	90,000-99,999	0 (0)	
	≥100,000	3 (27)	
**Employment status, n (%)**			
	Yes, full-time	3 (9)	
	Yes, part-time	4 (12)	
	No, retired	3 (9)	
	Other	1 (3)	
**Participant’s residence (county, Maryland or Ward, Washington, DC), n (%)**			
	Prince George’s County	6 (54)	
	Ward 5	3 (27)	
	Ward 7	2 (18)	

Mean areas varied by the size of the buffers (200 m, 400 m, and 800 m) and types of buffers based on residential (circular and line-based road network buffers) and GPS activity space (Table 5). As expected, the areas for a line-based road network buffer were smaller than that for a circular buffer. Areas for residential buffers (circular and network buffers) were also smaller than the GPS activity space areas. We plan to explore different sizes and types of buffers.

**Table 5 table5:** Mean areas for participants’ residential (circular and network) and GPS activity space buffers (N=11).

Type of buffer	Size (km^2^), mean (SD)		
	200 m	400 m	800 m
Circular buffer	0.13 (0)	0.50 (0)	2.01 (0)
Network buffer^a^	0.05 (0.02)	0.17 (0.08)	0.64 (0.33)
GPS activity space	20.48 (8.09)	53.32 (20.77)	123.02 (46.72)

^a^On the basis of a line-based road network buffer around the residence of a participant.

### Protocol Approval

Full support for this study has been received from the NIH IRB (ClinicalTrial.gov identifier NCT04014348).

## Discussion

### Principal Findings

This pilot study would contribute significantly to scholarship regarding the association between neighborhood social environment (eg, poverty and crime) and stress-related neural activity, a measure of chronic stress–related neural activity. This is important because there is limited research on this topic. This study is also novel because the relationships between neighborhood social environment conditions, detailed immune markers linked to physiological stress–related neural activity response, and vascular function are extremely understudied.

### Lessons Learned From Feasibility of GPS Use

When 11 participants from our study (ClinicalTrials.gov identifier NCT03288207) returned the GPS units to research staff members, GPS tracking was generally accepted. Pilot device testing revealed several concerns that will be addressed in this study. For instance, participants mentioned that they often forgot to charge the GPS device each night, as required by their limited battery life. They also sometimes forgot to bring the GPS with them when they left the house each morning.

For the overall study, we plan to address these device issues using the EMA app. The morning EMA prompt will include a message reminding participants to bring all of their devices, and the evening prompt will include a message reminding participants to charge their GPS units. These messages will hopefully curtail user errors and increase device compliance.

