### Devices

Participants will receive an accelerometer (ie, objective activity monitor; ActiGraph wGT3X-BT) to measure PA, sedentary time, and sleep duration for at least 14 days. The ActiGraph accelerometer has been previously used to objectively assess PA [23,24], sedentary time [23,24], and sleep duration [32] among adults. The data will be collected at 1-minute epochs. Two distinct cut-points based on approaches by Troiano [5] and Matthews [33] will be used to determine the intensity of PA. Participants will be instructed to wear the monitor on their dominant wrist with a wristband at all times, except when bathing or swimming. A valid day of accelerometer monitoring is defined as ≥10 hours of wear time [33]. The time-stamped recordings from the accelerometers will be linked with GPS data.

Participants will also receive a GPS unit (ie, tracking device, Qstarz BT-Q1000eX GPS Logger). The GPS unit receives a satellite signal to identify latitude and longitude coordinates for a given period. GPS units will monitor participants’ daily activities via locations where they travel throughout the day for at least 14 monitoring days. GPS units will also record distance, speed, elevation, and time. The data will be collected at 1-minute intervals. This device has been used successfully in a recent study [34]. This GPS device is small and can be worn on a belt or placed in a backpack or bag. It will provide a timestamp and GPS coordinates. A valid day of GPS tracking is defined as ≥10 hours of wear time [35].

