We will use a smartphone app to record EMA data via a mobile phone; these methods have been previously used for adults [36,37]. We will use two approaches for participants to record their PA, neighborhood environment, and stress. The first is an event contingency assessment. With this assessment, participants will be expected to record within the smartphone app when they engage in a certain behavior (eg, PA) within 15 minutes of the event occurring. The other type of assessment involves random survey prompts. Participants will respond to a series of questions on each day of the week. They will receive EMA random prompts for each assessment for that day (up to three random prompts for each assessment [morning, afternoon, and evening] and a maximum of nine prompts each day). The survey may take approximately 2-3 minutes to complete each time. Each item assesses the type of neighborhood context for the physical environment (eg, home, work, and outdoor), vegetation (amount of trees), traffic (amount of traffic), and safety (feeling safe and violence). Mood (positive and negative affect) and stressors (eg, daily hassles) from the EMA survey will be used specifically as psychosocial factors for each sub-aim. Previously validated EMA surveys and protocols for adults will be used in the proposed study [36,37].

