### Compliance

EMA compliance rates will be based on answered surveys divided by the total number of scheduled EMA surveys for each participant. We will also monitor participation rate, missing data, latency period (defined as the time between receiving EMA prompts and the items answered), and attrition rate [38]. In additionally, we will follow up each participant daily, irrespective of the compliance rate, to ensure that they do not have issues with device use. Basic statistical analyses will be performed to better understand participant compliance, such as compliance rate, missingness, participation rate, and latency period. In addition, as an exploratory analysis, the missingness of EMA surveys will be examined using pattern mixture random-effects modeling [39]. Furthermore, mindless EMA responses to surveys may occur. To address this issue, we have selected survey items that are crucial to our study aims to minimize participants’ burden.

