**Figure 5 figure5:**
[figure not shown]
GPS activity space buffers based on individuals’ daily paths.

In Table 3, real-time EMA measures will include perceived neighborhood social environment (eg, violence and safety), mood states (positive or negative affect [70]), perceived stress (eg, stressed and irritated [49]), and daily hassles (eg, work load [71]) with three random prompts within defined timeframes (7-9 AM, 11 AM-1 PM, and 5-7 PM) throughout the day (Table 3; Figure 6) [36]. Participants will initiate their own EMA recording when they start engaging in a certain activity (ie, event contingency; Table 3; Figure 6) [68,69]. The event contingency approach is based on a self-initiated response to behaviors and contexts. Participants will be instructed on how to initiate the EMA recording and respond to a certain activity and when to initiate their EMA recording. For example, when participants commute to work by car, they initiate it by themselves and record their mode of activity in the smartphone app. EMA measures will be merged with GPS activity space measures with the respective timestamps. Before the full pilot study, we tested GPS units and EMA using a smartphone app (ilumivu, Inc) to identify any potential barriers to use.

**Table 3 table3:** Random prompts and event contingency items for ecological momentary assessment.

Variable			Item		Response options

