### Merging Multiple Data

Complete master data will be created based on multiple data sources, including PA via accelerometers (ie, 1-minute epochs), GPS units (1-minute epochs), and EMA via a smartphone app (3 times/day). First, each recording of the GPS points will be linked to the respective time-stamped accelerometer data for each minute. Then, EMA data (three times through morning, afternoon, and evening assessments) will be linked to the corresponding GPS and accelerometer data. The complete data will then be collapsed by hours, time of day (morning, afternoon, and evening), and days.

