#### Limitations

This study had several limitations that need to be addressed. We may have some difficulties in recruiting African Americans residing in Ward 3, as the number of African American women living in Ward 3 is lower than that in Ward 5 in Washington, DC. However, our research group has strong relationships with organizations throughout Washington, DC, which will allow us to help with recruitment efforts in Ward 3. Furthermore, we will closely work with the recruitment liaison at the NHLBI at the NIH to resolve this issue. We should be able to recruit both White and African American female participants from Ward 5 from low-SES (household income of US $50,000-74,999 [about 15% of total residents in Ward 5]) to high-SES neighborhoods (household income of US $100,000-149,999 [about 15% of total residents in Ward 5]). In addition, this study has a cross-sectional design, thus limiting causal inference. Another limitation is that this study has a relatively small sample size (approximately 60 women) to assess differences in vascular function and immune cell activation based on exposure to adverse neighborhood social environment in Washington, DC. Note that the intent of this study is to establish feasibility and sample size needs for a larger study. We will also compare the extremes of neighborhood social factors to see if there are differences in vascular measures (eg, 5% highest poverty vs 5% lowest poverty) and assess racial differences in vascular inflammation and function within each ward. Finally, our analyses are at the person level, which do not intend to elucidate the within-day variability of PA and psychosocial factors in relation to biomarkers of stress. For a larger study, we plan to investigate the associations between within-day variability and outcomes.

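### The reminder to bring the GPS unit is sent at a random time between 7 and 9 AM, so for a woman who leaves home before 9 AM it can come too late

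*Protocol article*

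**What the plan says.** The Discussion section on lessons learned from GPS feasibility describes what happened when 11 women tested the device: "They also sometimes forgot to bring the GPS with them when they left the house each morning". It then gives the remedy for this study: "The morning EMA prompt will include a message reminding participants to bring all of their devices". A matching evening message asks participants to charge the unit.

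The timing is set in Methods, in the paragraph of the Exposures section that introduces Table 3. EMA items are collected "with three random prompts within defined timeframes (7-9 AM, 11 AM-1 PM, and 5-7 PM) throughout the day". The section on merging data agrees with one prompt per window, describing "EMA via a smartphone app (3 times/day". The Devices section allows more: "up to three random prompts for each assessment [morning, afternoon, and evening] and a maximum of nine prompts each day".

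Other provisions bear on the point:

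- On carrying the unit, the Devices section says: "This GPS device is small and can be worn on a belt or placed in a backpack or bag".
- On support, the Compliance section says: "we will follow up each participant daily, irrespective of the compliance rate, to ensure that they do not have issues with device use". It gives no time of day for this contact.
- On the unit of analysis, the Limitations section says: "our analyses are at the person level".

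**The concern.** The failure happens at one moment, when the woman walks out of the door. A reminder helps on that day only if it reaches her before then. A prompt drawn at random from a two-hour window suits the sampling of mood and stress but not this purpose, because its timing is unrelated to departure. The article states both the carrier of the message and the timing of that carrier, and the two do not fit.

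What is at stake is the quality of the GPS data. A unit that is running but left at home records home while the woman is elsewhere. GPS activity space is one of the two exposure types, and the study uses it to avoid the limits of home-based measures. This error pulls the measure back towards home. The wrist accelerometer still travels with her and is linked to GPS minute by minute, so activity elsewhere would be placed at home. A valid GPS day needs at least 10 hours of wear. If wear is judged from logged hours, which the article does not specify, such a day could pass as valid.

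The sample size section also names GPS feasibility for a larger study as a purpose of the pilot, so a reminder that often misses its moment would affect what is learned about compliance. The evening charging message comes before the action it asks for and raises no such problem.

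**Working it through.** The plan gives no figure on this point, so there is none to reproduce. The check asks how often the message would come after departure, and how many days that could affect.

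**Inputs from the article**

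- Morning window: 7 to 9 AM, random (Exposures).
- Morning prompts: one (Exposures; Merging Multiple Data), or up to three (Devices).
- Monitoring: at least 14 days (Devices).

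**Assumptions, because the article gives no values**

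- The prompt time is uniform over the window.
- Departure hour d ranges from 7:00 to 9:00.
- Early departures occur on the 10 weekdays in 14 days.
- Without a timely reminder, the unit is forgotten on a share f = 5%, 10% or 30% of those days, independently of the prompt time.

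**Step 1: chance that the message is late**

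One prompt: P = (9 − d)/2, limited to the range 0 to 1. With three independent prompts that all carry the message, it is too late only if all three come after departure, which has probability P³.

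| Departure | One prompt | Three prompts |
|---|---|---|
| 7:00 or earlier | 100% | 100% |
| 7:30 | 75% | 42% |
| 8:00 | 50% | 12.5% |
| 8:30 | 25% | 1.6% |
| 9:00 or later | 0% | 0% |

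For example, at 8:00 P = (9 − 8)/2 = 0.50, and 0.50³ = 0.125.

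**Step 2: expected unprotected days per woman**

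A day is beyond the reminder's reach only if the unit is forgotten and the message is late. The expected number is 10 × f × P. For one prompt:

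| Departure | f = 5% | f = 10% | f = 30% |
|---|---|---|---|
| 7:00 | 0.50 | 1.0 | 3.0 |
| 7:30 | 0.375 | 0.75 | 2.25 |
| 8:00 | 0.25 | 0.5 | 1.5 |
| 8:30 | 0.125 | 0.25 | 0.75 |
| 9:00 | 0 | 0 | 0 |

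At 8:00, as a share of 14 days: 0.25/14 = 1.8%, 0.5/14 = 3.6% and 1.5/14 = 10.7%.

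With three prompts at 8:00, the expected number is 10 × f × 0.125 = 0.06, 0.13 and 0.38 days.

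For a given f, these are the most that a better-timed message could save. They take no account of daily follow-up, habit or keeping the unit in a bag.

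**The case against.** The strongest objection is that this is operational detail. Two sentences in a Discussion section say which prompt carries which message. Whether windows are set for each participant, or the message is shown at the start of the window, would normally be found in the full protocol or the app configuration. The article also claims little, expressing only the hope that the messages will reduce user errors. A message that is timely on many mornings does that, and even a late one may build a habit over two weeks.

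On size, up to three prompts may fall in the morning window, which lowers the risk sharply. Departure times and forgetting rates are assumed. The forgetting was reported by 11 women with a mean age of 56 in another study, while this one enrols ages 19 to 45. Staff contact each participant daily, the unit can stay in a bag, and person-level analysis over at least 14 days dilutes a bad day. A still GPS unit alongside an active wrist monitor could be noticed, although no such check is stated. The ward comparisons, residential exposures and sample size are untouched, and an extra alert adds burden.

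Most of this stands as a limit on size. It does not remove the point. The article is not silent: it states the carrier and the random window, and mentions no earlier reminder. Wording that allows up to three prompts sets no minimum, and the remedy refers to a single morning prompt. Three prompts would not help a woman who leaves at or before 7:00. The daily follow-up is not described as a reminder before departure. The unit needs charging every night, so it may well be out of the bag in the morning, though that is inference.

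**Conclusion.** The point holds as a minor, cheaply corrected weakness in a stated remedy. For every departure before 9 AM there is a chance above zero that the reminder comes after the event it is meant to prevent, whether one or three morning prompts are sent. That chance depends only on the stated window and the assumption of a uniform random time within it.

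The number of days affected is much less certain, because it rests on assumed departure times and forgetting rates. It may be near zero in women aged 19 to 45 who keep the unit in a bag. No error rate, sample size or ward comparison is affected. What could suffer is the accuracy of the GPS activity-space exposure on some days, and the evidence on GPS compliance that the pilot is meant to supply.

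**What to change.** At device hand-out on the first visit, ask each woman when she usually wakes or leaves home. Send the message about the devices as a fixed notification shortly before that time, needing no answer. Leave the random EMA prompts as they are, so the sampling of mood and stress does not change.

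The cost is one question, a minor app setting and one brief alert a day on top of at most nine prompts. The alert will still miss days when she leaves unusually early.
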